**Alert criteria for blood tests**

| Test       | Value out of reference range:                                                                                                                                                                                                         | Value may be medically significant                                                                                                                                                                         | Value requires immediate notification                                                                                                                                                                                                                   |
|-------------------|----------------------------------------------------------------------------------------------------------------------------------------------------------------------------------------------------------------------------------------------|-------------------------------------------------------------------------------------------------------------------------------------------------------------------------------------------------------------------|----------------------------------------------------------------------------------------------------------------------------------------------------------------------------------------------------------------------------------------------------------------|
|                   | Participant should be notified at a routine visit or within two weeks by a qualified staff member that the value is out of the normal range for all adults but may or may not be medically important and could be discussed with PCP. | Participant should be notified at a routine visit or within two weeks by a qualified staff member that the value is potentially medically significant and strongly recommend that it be discussed with PCP | A qualified staff member should contact the participant within one working day and request permission to contact a PCP. Assuming that the participant has normal vital signs and is feeling well, there is no need to invoke emergency medical systems. |
| Triglycerides     | >199                                                                                                                                                                                                                                         |                                                                                                                                                                                                                   |                                                                                                                                                                                                                                                                |
| Total cholesterol | >199                                                                                                                                                                                                                                         |                                                                                                                                                                                                                   |                                                                                                                                                                                                                                                                |
| HDL               | <40                                                                                                                                                                                                                                          |                                                                                                                                                                                                                   |                                                                                                                                                                                                                                                                |
| Hemoglobin        | M <13 or > 16
F <12 or > 15                                                                                                                                                                                                               | M < 12 or > 16.5
F < 11 or > 16                                                                                                                                                                                | < 8 or > 18                                                                                                                                                                                                                                                    |
| WBC count         | < 4000 or >11000                                                                                                                                                                                                                             | < 3000 or > 12000                                                                                                                                                                                                 | < 2000 or > 20000                                                                                                                                                                                                                                              |
| Platelet count    | < 130000 or > 400000                                                                                                                                                                                                                         | < 100000 or > 500000                                                                                                                                                                                              | < 30000 or > 1000000                                                                                                                                                                                                                                           |
| Sodium            | < 135 or > 146                                                                                                                                                                                                                               | < 130 or > 155                                                                                                                                                                                                    | < 125 or > 160                                                                                                                                                                                                                                                 |
| Potassium         | < 3.5 or > 5.3                                                                                                                                                                                                                               | < 3.0 or > 5.7                                                                                                                                                                                                    | < 2.6 or > 6.2                                                                                                                                                                                                                                                 |
| Calcium           | <8.5 or > 10.3                                                                                                                                                                                                                               | < 8.0 or > 11.5                                                                                                                                                                                                   | < 7.0 or > 13.0                                                                                                                                                                                                                                                |
| Glucose           | < 70 or > 125                                                                                                                                                                                                                                | < 60 or > 140                                                                                                                                                                                                     | < 50 or > 400                                                                                                                                                                                                                                                  |
| BUN               | > 30                                                                                                                                                                                                                                         | > 40                                                                                                                                                                                                              | > 80                                                                                                                                                                                                                                                           |
| Creatinine        | > 1.4                                                                                                                                                                                                                                        | M >2.0
F > 1.6                                                                                                                                                                                                 | > 3.5                                                                                                                                                                                                                                                          |
| Albumin           | < 3.5                                                                                                                                                                                                                                        | < 3.0                                                                                                                                                                                                             |                                                                                                                                                                                                                                                                |

**8.4. Safety Considerations for the Physical Activity Intervention**

Appropriately designed and implemented physical activity interventions have been shown to be safe and efficacious in older adults. The literature on physical activity training in the frail elderly in nursing homes contains no reports to date of serious cardiovascular incidents, sudden death, myocardial infarction, or exacerbation of metabolic control or hypertension. Also, LIFE researchers have conducted over 26,000 assessments of maximal dynamic strength without one single cardiovascular event. A recent review concluded that an appropriately prescribed resistance physical activity program is a safe form of physical activity for the majority of the population and is associated with minimal risk of cardiovascular events, even in those with previous myocardial infarction or chronic congestive heart failure.

#### 8.4.1. Pre-Physical Activity Safety Screening

To maximize the **participants' safety** we follow a standardized screening protocol (Figure 8.4.1.). Accordingly, all potential participants undergo **screening for cardiovascular and other major diseases** by means of a health questionnaire, medication inventory, ECG and physical exam, which are initially collected and reviewed by a qualified health professional such as a nurse practitioner or physician assistant. In cases where there are no potential alert values on any of the forms and no unexpected or unusual symptoms or conditions, the qualified health professional may approve performance of the 400 meter walk. In all other cases, the study physician must review and approve the participant for performance of the 400 meter walk. Those with overt cardiovascular diseases (or other severe diseases) that meet the exclusion criteria as determined by the study physician are excluded. Prior to randomization of a potential participant, all medical information must be reviewed by a study physician, who is ultimately responsible for determining study eligibility and approving randomization. Next, otherwise eligible persons undergo the **400 m walk** test. According to a protocol to evaluate cardiovascular reserve similar to the one suggested by Gill et al., persons who develop chest pain or substantial shortness of breath during the 400 m walk test are also excluded. Those who are not excluded are randomized to the physical activity intervention group or to the successful aging program.

**Figure 8.4.1. Algorithm for screening morbid conditions**

[figure not shown]

**Participants do not undergo physical activity stress testing.** This decision is based on the following considerations:

- The **recommendations** published by Gill et al. advised that a screening protocol based on a simple cardiovascular reserve test, similar to the one described above is more suitable for screening older adults than a protocol based on stress physical activity testing.
- The American Heart Association (AHA) and the American College Sports Medicine (ACSM) **joint position statement** advised that “apparently healthy persons of all ages and asymptomatic persons at increased risk may participate in moderate-intensity physical activity without first undergoing a medical examination or a medically supervised, symptom-limited physical activity test.”
- The **AHA Scientific Statement** on Exercise Standards for Testing and Training by Fletcher et al., advised that “for older, apparently healthy persons desiring to participate in a low to-moderate intensity activity such as walking, an exercise test may not be required”, and that “the role of exercise testing among the elderly (>75 years) as a guide to identifying the high-risk patient for primary prevention requires further study”.
- The majority of older persons (>75%) are **unable to satisfactorily complete** a treadmill exercise test, which makes its utility as a screening tool in the elderly population questionable.
- Older persons have a **high prevalence of ECG abnormalities**, which diminish the diagnostic accuracy of treadmill exercise testing.
- Participants with potential cardiac contraindications to the physical activity program are identified and excluded by means of the **screening** process described above.
- Physical activity of **moderate intensity** is conducted in a **supervised environment**.
- A maximal or near maximal exercise test on a treadmill is an **unpleasant, if not frightening experience**, for sedentary and unfit adults (unpublished data from WFUHS and Cooper Institute). Requiring an exercise stress test may deter older persons from participating in the trial.
- Regular exercise and physical activity **may actually reduce the overall risk of MI and death** among older persons, possibly through improvements in cardiac risk factors and overall fitness.

**In summary**, exercise stress testing provides little additional information, is not necessary to protect the safety of participants, and is disliked by sedentary and unfit participants. The physical activity intervention protocol also requires that the center-based sessions at the beginning of the study include careful monitoring of cardiac and other signs and symptoms by trained staff.

#### 8.4.2. Safety Measures During Physical Activity

Center based interventions are conducted at a central location and all sessions are conducted and supervised by **trained interventionists**, who monitor potential adverse experiences and symptoms. During the physical activity sessions a defibrillator and on-site trained staff are available to deal with medical emergencies. Also, institutional and community EMS services are activated if needed. As indicated previously, participants are taught the importance and proper method of **warming-up** prior to and **cooling-down** following structured activity sessions. If at any point during a physical activity session, participants develop chest pain, shortness of breath, or dizziness, they are instructed to rest and to contact the center and their physicians if these symptoms persist or recur with further physical activity. The implementation of the physical activity sessions is consistent with the recommendations published by Fletcher et al. for older adults who may have

stable cardiovascular disease.

Blood pressure and heart rate are monitored before and after the walking activity at each center-based intervention session. Blood pressure and heart rate are measured during the walking at each center based session in participants who had experienced any of the following at a previous physical activity session:

- Resting blood pressure systolic  $\geq 200$  mm Hg or diastolic  $\geq 100$  mm Hg
- Decrease in systolic blood pressure  $\geq 20$  mm Hg following the activity
- Increase in systolic blood pressure to  $\geq 250$  mm Hg or in diastolic blood pressure  $\geq 115$  mm Hg following the activity
- Resting heart rate  $\geq 120$  beats/min or  $\leq 45$  beats/min
- Increase in heart rate  $\geq 90\%$  of age predicted maximum
- Unusual or severe shortness of breath
- Chest pain or discomfort, or heartburn
- Palpitations
- Light headedness, dizziness or feeling about to faint
- A physical activity session had to be discontinued because of other symptoms, excluding musculoskeletal symptoms (e.g., knees, ankles, hips), reported by the participant.

If any of the above occurs, the individuals are instructed to seek their physician's permission before continuing with the physical activity program.

Very few persons are expected to drop out for this reason based on previous experience and cardiac-based exclusion criteria.

Procedures to minimize discomfort include **warm-up and cool-down activities** that include light walking or cycling and flexibility exercises. The participants are also introduced to the intervention activities in a structured way, such that they begin with **lighter resistance and gradually increase** over the course of the first 2-3 weeks of the intervention. During the intervention visits, participants are **supervised at all times and instructed** on correct physical activity techniques. Participants are instructed to talk with the interventionists about any muscle soreness.

If for any reason the participant reports an injury, chest pain, shortness of breath, or dizziness, they are referred to their doctor, or the study clinician calls the doctor or other health care provider. The participating institutions are in compliance with NIH policies regarding physical injuries resulting from experimentation of human subjects. Trained technicians administer all tests, with an emphasis on the well being of the participant. In addition, specific criteria for **suspending or stopping physical activity** are developed to adjust the program for **intercurrent illness**.

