### 7.2.1 Contact Mode and Frequency

The physical activity intervention consists of a general weekly walking goal of 150 minutes. This is consistent with the public health message from the 2008 Physical Activity Guidelines for Americans report that moderate physical activity should be performed for 30 minutes on most if not all days of the week (150-210 total minutes). This goal is **approached in a progressive manner** across the first 3 months of the trial. There are multiple ways that the goal can be achieved, based on the physical abilities and constraints of each participant. In light of the heterogeneity of the target population (with respect to physical capabilities and health status), this study will specifically define the variability in participants' ability to reach this weekly target, to estimate the dose-response relationship between incremental increases in weekly physical activity and changes in the primary and secondary outcomes, and to better specify the level of ongoing behavioral instruction needed to achieve such changes.

| Table 7.2.1. Intervention staff contacts for physical activity group |                                |                                                                                          |
|-----------------------------------------------------------------------------|--------------------------------|------------------------------------------------------------------------------------------|
| Week                                                                        | Center-Based Physical Activity | Home-Based Physical Activity                                                             |
| Adoption: weeks 1-52                                                        | 2 times each week              | 1 time/week (weeks 1-4)
2 times/week (weeks 4-8)
Up to 3-4 times/week (weeks 8-52) |
| Maintenance: weeks 53 – end                                                 | 2 times each week              | Up to 3-4 times/week                                                                     |

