## 8. Participant Safety and Confidentiality

The study monitors the medical safety of participants. One aspect of this monitoring is to evaluate potential volunteers at screening to determine whether it is safe for them to participate in the planned intervention. Another aspect is monitoring of safety during study assessments. A third area is safety during physical activity, both supervised and unsupervised. Also, if a volunteer has a medical or surgical illness, the safety of continuing or resuming participation in interventions is ascertained by the medical staff at the local center in cooperation with the participant's primary care physician. Finally, the study monitors adverse events, assess their potential relationship to the intervention and report events to the Data Safety Monitoring Board (DSMB).

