## 8.5. Adverse Events

**Serious adverse events** in LIFE are defined to include: death, a life-threatening adverse experience, inpatient hospitalization or prolongation of existing hospitalization, a persistent or significant disability/incapacity, or a clinically significant laboratory or clinical test result. Important medical events that may not result in death, be life-threatening, or require hospitalization may be considered serious adverse experiences if they might jeopardize the participant or might require medical or surgical intervention to prevent one of the outcomes in the definition. An example of this in LIFE is an injurious fall resulting in a fracture that occurred during walking for physical activity.

For LIFE purposes, an **adverse event or experience** is defined as any health-related unfavorable or unintended medical occurrence that happens during the process of screening or after randomization. Certain adverse events may be protocol-defined outcomes (serious fall injury). Minor adverse events are defined as conditions that may be

unpleasant and bothersome to the participant, such as sore muscles, but that do not require discontinuing the study intervention or components of the intervention. Examples of minor adverse events include but are not limited to the following: anxiety, fatigue, decreased appetite, insomnia, dizziness, muscle or joint stiffness, muscle strain or soreness, ankle or knee pain, foot pain, and other minor symptoms that may have restricted the participant's usual activities for at least ½ day like a head cold, flu or allergy problems. Minor adverse events should be reported on an annual basis to each site's own IRB.

Potential adverse events for study related activities and interventions are explained to each participant by trained study personnel during the informed consent process. Each participant is instructed to report the occurrence of an adverse event at scheduled data collection times (scheduled clinical exams or phone interviews). Participants also have access to study clinic personnel at other times to report serious adverse events or concerns about the safety of participating in the LIFE Study.

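### Section 8.4.2 gives two conflicting instructions for a first episode of chest pain or dizziness during exercise that clears with rest (minor).

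*Protocol*

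**What the plan says.** Section 8.4.2 contains three statements on symptoms during intervention exercise.

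- **Opening paragraph.** A participant who develops chest pain, shortness of breath or dizziness in a session is covered by this: "they are instructed to rest and to contact the center and their physicians if these symptoms persist or recur with further physical activity".
- **Event list and the rule after it.** The list identifies participants whose blood pressure and heart rate are to be measured while they walk, because of something that happened at an earlier session. It includes "Chest pain or discomfort, or heartburn" and "Light headedness, dizziness or feeling about to faint". Shortness of breath is listed only when it is out of the ordinary or severe. The rule that follows covers any listed event and tells the participant to seek the physician's "permission before continuing with the physical activity program".
- **Closing paragraph.** "If for any reason the participant reports an injury, chest pain, shortness of breath, or dizziness, they are referred to their doctor"; alternatively, the study clinician calls the doctor or another provider.

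The introduction to Chapter 8 shows that its scope is wider than the center: "A third area is safety during physical activity, both supervised and unsupervised".

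**The concern.** The first two statements attach different conditions to the same symptoms. The opening sentence requires contact only if the symptom continues or comes back on further exertion. The rule after the list requires permission once the symptom has occurred at all. A participant who follows the opening sentence could resume exercise after a brief episode of chest pain without telling anyone. A participant who follows the later rule could not.

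At stake is a safety instruction for people aged 70 to 89 who enter without exercise stress testing (section 8.4.1). During a home session the participant acts alone, so the instruction that he or she was given decides what happens next.

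**Working it through.** The protocol states no figure on this point and no calculation applies. The check sets the instructions side by side and applies each to defined cases.

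**Inputs**

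- A: opening paragraph of 8.4.2 (contact if the symptom persists or recurs).
- B: rule after the event list in 8.4.2 (permission after any listed event).
- C: closing paragraph of 8.4.2 (referral, or a call to the doctor, once reported).

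**Step 1. Apply each instruction**

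| Case | A | B | C |
|---|---|---|---|
| Chest pain or dizziness, does not settle | Rest, contact center and physicians | Permission needed | Referral if reported |
| Chest pain or dizziness, first episode, settles with rest | Rest; no contact unless it returns | Permission needed | Referral if reported |
| Shortness of breath, unusual or severe, settles with rest | Rest; no contact unless it returns | Permission needed | Referral if reported |
| Other shortness of breath, settles with rest | Rest; no contact unless it returns | Not listed | Referral if reported |

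In the first row A and B are compatible. In the second they differ, and that is the point raised here. The third row shows the same difference, so shortness of breath overlaps only in part. In the fourth, B does not apply.

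**Step 2. Does A imply that exercise resumes?** A's second trigger is a symptom that returns on further exertion. It can be met only if the participant has started again. For the second row, then, A most naturally describes rest followed by more exercise, with no contact in between.

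**Step 3. Does another passage settle it?**

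- C leans toward B. It depends on a report, though, and does not say that activity is held in the meantime.
- Section 7.4.4(c) suspends activity that is specifically limited by chest pain or dyspnea until there is definitive treatment. It does not mention dizziness and does not address a brief episode that clears. It has its own trigger and is not in conflict with A or B.
- The lead-in to the list speaks of an earlier session and introduces a monitoring rule, so even the starting point of B is not fully clear.
- No sentence gives A or B precedence, or confines A to home sessions and B to center sessions.

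**Step 4. Which instruction fits the rest of the protocol?** Section 8.3 stops the 400 m walk test for chest pain or for feeling faint, lightheaded or dizzy, without asking whether the symptom persists. Sections 4.2.2 and 8.4.1 exclude anyone who develops chest pain on the screening walk. A is the outlier; B and C match the protocol's own standard.

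**The case against.** The strongest reply is that A and B answer different questions: A is what to do within the session, and B is the rule for going on with the program. A participant could obey both by resting now, calling if the symptom continues, and obtaining permission before going on. A related reading assigns A to home and B to the center. Either is possible, but the protocol states neither, and the session-versus-program reading fits poorly with A's reference to recurrence on further exertion.

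Operating detail may also sit in the manual of operations or the intervention manual, which are not at hand. That may narrow the problem in practice, but it does not remove a conflict between two rules in the protocol itself.

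Two stronger readings are tempting, and the documents do not support them.

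- **Home episodes would go unreported for a long time.** A reader might infer this from section 8.5: "Each participant is instructed to report the occurrence of an adverse event at scheduled data collection times". But participants are offered two center sessions a week throughout (Table 7.2.1, section 7.2.5). Staff enter daily activity from the logs weekly (7.2.2). Participants report those logs at intervention visits, and discomfort is monitored on them (7.4.2, items 8 and 10). Section 8.5 itself provides that events reported to any staff member at any time go to unmasked medical staff. For an attending participant the opportunity to report comes within days.
- **The planned home sessions measure the size of the problem.** Table 7.2.1 counts sessions, and only as an upper limit from week 8. It says nothing about how often a transient symptom occurs.

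One part of the objection stands in full. Section 8.5 gives dizziness as an example of a minor adverse event, a class that does not call for discontinuing the intervention. Applying B to every episode of dizziness therefore has a real cost in holds.

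**Conclusion.** The conflict is real and confined to section 8.4.2. For a first episode of chest pain or dizziness that clears with rest, one instruction asks for no contact and the other requires physician permission before the program continues. This is two written rules that disagree, not missing detail.

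Severity is minor. Center sessions are constantly supervised, with a defibrillator, trained staff and emergency services available. A home episode would usually come to light within days and trigger the referral in the closing paragraph of 8.4.2. That assessment assumes that the participant attends center sessions and mentions the episode or logs it. The number of episodes cannot be derived from the documents. Nothing here bears on the primary estimate, power or type I error.

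**What to change.** Reword the opening sentence of 8.4.2 so that it applies the permission rule already stated after the list, for center and home sessions alike:

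- Chest pain, dizziness, or unusual or severe shortness of breath means stop, rest and tell the center. The program is not resumed until the participant's physician gives permission.
- If the symptom persists at rest, emergency services are activated or the center and physician are contacted at once.
- Other shortness of breath is reported and referred, as the closing paragraph of 8.4.2 already provides.

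A cross-reference to 7.4.4(c) would help but is optional.

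The cost is one reworded sentence and a retraining note so that interventionists give all participants the same instruction. No new staff or procedure is needed. The downside is some additional short holds, mainly for dizziness. Their number is unknown because the protocol gives no symptom frequency. Section 8.4.2 itself expects very few participants to drop out because of the permission rule.
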